### 3.4 What are the proposed methods for protecting against sources of bias?

Both study products will be blinded to participating families and all researchers. Euro-Pharm will provide these supplements *in kind* in identical containers and the supplement will be identical in color, taste, texture etc. Each bottle will have a unique code to enable tracing back to the product dosage in the rare situation of an adverse event without unblinding the study. Euro-Pharm will provide the blinding codes in sealed envelopes, a copy each for the PI and the medical team. The allocation will be at the end of the baseline visit and care-givers will be educated by a nurse on how to properly give the supplement.

### 3.5 What are the inclusion/exclusion criteria?

For **screening**, inclusion criteria is any healthy term born infant of appropriate weight for gestational age (AGA) based on a Canadian growth reference [1] and born to a generally healthy mother of any race. For the randomized trial, infants must have serum 25(OH)D <50 nmol/L; and for those in the reference group >50 nmol/L. For both the trial and reference groups other **inclusion criteria** are: born to mothers with otherwise healthy pregnancy free of medications that impact vitamin D metabolism (except vitamin/mineral supplements) or fetal growth and intent to breastfeed to at least 3 mo. For the trial we will not exclude on the basis of maternal pre-pregnancy BMI, but will document pregnancy weight gain and obstetrical history from the medical record. For the healthy reference group we will recruit from our screening pool only infants born to mothers of healthy weights (pre-pregnancy BMI 18.5-24.9 kg/m^2) and weight gain according to IOM criteria [2]. **Exclusion criteria** are maternal smoking in pregnancy as it limits growth; and diabetes, preeclampsia, celiac disease, inflammatory bowel disease etc. and medications that impact vitamin D/mineral metabolism. All maternal medications will be documented.

### 3.6 What is the proposed duration of treatment period?

Trial is 1 wk to 12 mo of age; follow-up to 3 y.

### 3.7 Frequency and duration of follow up:

Baseline (1 wk), 3, 6 and 12 mo for the trial; then 2 and 3 y.

### 3.8 Primary and secondary outcomes:

Primary outcome: lean mass during the trial; with follow-up thereafter to 3 y. Secondary outcomes: body composition including bone mass and BMI z-scores, tissue accretion rates across the study period and follow-up; vitamin D status and mechanistic explanations (IGF-1).

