## 2. Trial objectives

Primary Trial Objective: To test whether rapid correction of vitamin D status early in the neonatal period results in greater lean mass by 3 mo of age and sustained to 3 y. It is hypothesized that neonates with low vitamin D status and provided a vitamin D supplement of 400 IU/d will have lower accretion of lean mass by 3 mo of age and thereafter to 3 y compared to infants given 1000 IU/d.

Secondary Trial Objectives are designed *a priori* to test:

1) Whether correction of low vitamin D status early in infancy using 1000 IU/d of vitamin D normalizes body composition (lean, fat, bone mass) across infancy and to 3 y of age;

Tertiary Objective: outside of the trial, establish a healthy reference group with good neonatal vitamin D stores ( $>50$  nmol/L 25(OH)D) and given the AI of 400 IU vitamin D/d with all of the same measurements as the trial since these are not all available (e.g. IGF-1, IGFBP3 using same assays). The reference group will be frequency matched to trial infants based on skin color of the infants and season.

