### 3.11 What is the proposed sample size and what is the justification?

The minimum sample size (n=66) is based on the primary objective, lean mass in g at 3 mo of age and an effect size of 9% (400 g), SD of 670 g, an allocation ratio of 1:1, power of 80 and alpha of 0.01. Accounting for possible dropouts ( $\leq 10\%$ ) or missing data (1% due to movement artifact) we will study 74 infants/group. The attrition is based on 3 similar studies with an average attrition of 9% [3, 15, 16]. We have used a more stringent estimate based on an alpha of

1% to enable multiple comparisons over time and in the event of greater variability in lean mass. We believe the estimated effect size is clinically meaningful since infants in the preliminary healthy status group treated with 400 IU/d increased lean mass between 1 mo and 3 mo by 670 g and the  $\Delta$  400 g anticipated between our trial groups by 3 mo represents 60% of that normal change which would be enough to reset growth for a leaner body phenotype.

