### 3.17 What is the proposed frequency of analyses?

For the primary outcome, one analysis will be conducted on blinded groups after all infants have completed 12 mo of study and a second analysis again at 3 y. We wish to keep all of the staff blinded across the entire study. This can be accomplished by generating a database of participants and by removing dates of birth and dates of visit.

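### The primary lean-mass endpoint is stated inconsistently across the protocol, and the 80% power was calculated for only one version, the 3-month level at two-sided alpha 0.01

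*Protocol*

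**What the plan says.** All references are to the protocol.

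- **Section 2, primary objective.** Rapid correction of vitamin D status is to be tested for whether it "results in greater lean mass by 3 mo of age and sustained to 3 y". This concerns the level of lean mass.
- **Section 2, hypothesis.** Infants given 400 IU/d "will have lower accretion of lean mass by 3 mo of age and thereafter to 3 y compared to infants given 1000 IU/d". This concerns change.
- **Section 3.8.** "Primary outcome: lean mass during the trial; with follow-up thereafter to 3 y". The secondary outcomes include "tissue accretion rates across the study period and follow-up".
- **Section 3.6.** "Trial is 1 wk to 12 mo of age; follow-up to 3 y". So the section 3.8 outcome runs from 1 week to 12 months.
- **Section 3.11.** "The minimum sample size (n=66) is based on the primary objective, lean mass in g at 3 mo of age". The inputs are a 400 g difference, SD 670 g, 1:1 allocation, 80% power and alpha 0.01. The strict alpha is justified partly by multiple comparisons over time.
- **Section 3.16.** The primary outcome goes into a mixed model with dosage, time and their interaction. Tukey-Kramer post-hoc tests follow, over two treatment groups, one reference group and four time points, at p < 0.05.
- **Section 3.17 (frequency of analyses).** The primary outcome is analysed once all infants have completed 12 months, with "a second analysis again at 3 y".

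**The concern.** A primary endpoint needs one variable, one time (or one defined summary over time) and one deciding test. Here the variable is a level in sections 3.8 and 3.11 and in the objective, but a change in the hypothesis. The time is 3 months, or 1 week to 12 months, or 3 months with persistence to 3 years. The deciding test could be a 3-month contrast, a dosage or dosage-by-time term, any of several post-hoc contrasts, or either of two analyses.

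This is not detail that a statistical analysis plan could supply. No such plan can satisfy sections 2, 3.8 and 3.11 together while they disagree.

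Supplementation stops at 12 months, so an early effect that later fades is a plausible result. It would be a success on the section 3.11 endpoint and would fail the durability part of the section 2 objective. If the choice is left until the data are seen, the main claim loses its confirmatory standing.

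**Working it through.** **1. Reproduce the stated sample size.** Inputs from section 3.11: difference 400 g, SD 670 g, alpha 0.01, power 80%. Sidedness is not stated; two-sided reproduces the figure, while one-sided would give 57.

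n per arm = 2 × SD² × (z₀.₉₉₅ + z₀.₈₀)² / difference² = 2 × 670² × (2.576 + 0.842)² / 400² ≈ 65.5, so 66.

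Power check: SE = 670 × √(2/66) = 116.6 g; 400/116.6 = 3.430; Φ(3.430 − 2.576) = 80.3%. The exact t-test gives 79.1%, a trivial difference. Dropout: 66/0.90 = 73.3, so 74. The stated figures stand.

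**2. What the 80% applies to.** It applies to the level at 3 months, tested once at two-sided 0.01. At the 0.05 level named in section 3.16, a single unadjusted test of the same endpoint would have Φ(3.430 − 1.960) = 92.9%. The power statement therefore depends on fixing both the endpoint and the alpha.

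**3. Other versions at alpha 0.01, 66 per arm.** The protocol gives no SD at other visits and no between-visit correlation, so these are assumptions shown as ranges.

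- *Accretion from baseline to 3 months.* SD of change = √(670² + s₀² − 2·r·670·s₀). With baseline SD s₀ of 300–670 g and r of 0.3–0.7, power is 63–99%.
- *Average over 3, 6 and 12 months.* SE of the average difference = √(2/66) × SD of an infant's three-visit average. Three SD sets at 3, 6 and 12 months were used (670/670/670, 670/750/850 and 670/800/950 g), with adjacent-visit correlation 0.5–0.85, multiplied along the visit sequence. If the full 400 g persists, power is 68–97%.

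Power can therefore lie on either side of 80%.

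**4. An illustrative fade.** Suppose the difference is 400, 300 and 200 g at 3, 6 and 12 months. The average effect is (400 + 300 + 200)/3 = 300 g.

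| Assumptions | SE of average | Power, average | Power, 3 months | The two tests disagree |
|---|---|---|---|---|
| SD 670 g throughout, correlation 0.5 | 91.2 g | Φ(300/91.2 − 2.576) = 76% | 80% | 17% |
| SDs 670/800/950 g, correlation 0.85 | 131.2 g | Φ(300/131.2 − 2.576) = 39% | 80% | 42% |

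The disagreement figures come from simulating the visit differences as multivariate normal. They are the lowest and highest over the nine combinations of SD set and correlation (0.5, 0.7, 0.85). In the second row almost all disagreements are trials significant at 3 months but not on average. Some disagreement is ordinary sampling variation: with a persistent 400 g the same two tests disagree in 9–17% of trials.

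If the fade continues to zero by 36 months, the section 2 durability claim is false by construction, while the 3-month test still succeeds in about 80% of trials.

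**The case against.** The strongest reply is that the sections can be read as one coherent design: lean mass measured repeatedly from 1 week to 12 months, sized at the first post-baseline visit, with 24 and 36 months as durability follow-up. Section 3.11 ties the primary objective to a variable, a unit and a time. Section 3.8 puts everything after 12 months under follow-up and makes accretion secondary. Section 3.16 models the outcome in this way.

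Much of this stands. Section 3.8 does settle level against change within the outcome list, and the 3-month reading is reasonable. But section 3.8 names no visit, section 2 keeps both accretion and 3-year persistence inside the primary objective, and nothing names the deciding contrast or analysis.

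A reader might go further and infer three things that the protocol does not support:

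- *That the trial is underpowered for its primary objective.* Very low figures appear only if significance is required separately at 3 and 36 months and the 36-month SD is well above 670 g. Section 2 states no such rule, and the protocol gives no such SD.
- *That the false-positive rate is 12–16%.* That range comes from taking the best of four versions at an unadjusted 0.05. It ignores the planned Tukey-Kramer correction and counts accretion, which section 3.8 makes secondary. At 0.01 the same exercise gives about 3%.
- *That the sample size is wrong.* It reproduces.

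**Conclusion.** The inconsistency is real and should be corrected, because the plan cannot be followed as written: sections 2, 3.8 and 3.11 describe different primary endpoints, and sections 3.16 and 3.17 do not say which result decides. This conclusion rests on the text alone.

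Its practical size is conditional. The 80% power is correct for the 3-month level at two-sided 0.01 and was calculated for nothing else. For other versions the power could be higher or lower, depending on SDs, correlations and persistence that the protocol does not give. The 17–42% disagreement illustrates one assumed fade and one reading of section 3.8 as an average over the three post-baseline visits. It is not a prediction.

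**What to change.** Use one definition in sections 2, 3.8, 3.11, 3.16 and 3.17 (frequency of analyses), namely the one the trial is sized on:

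*Primary endpoint: whole-body lean mass (g) at 3 months, 1000 versus 400 IU/d, estimated as the 3-month treatment contrast from the mixed model and tested once at two-sided alpha 0.01, in the analysis done when all infants have completed 12 months.*

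Then:

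- Make lean mass at 6, 12, 24 and 36 months and the accretion rates secondary, and reword section 2 so that persistence to 3 years is a secondary durability objective.
- In section 3.16, separate the primary contrast at 0.01 from the Tukey-Kramer comparisons at 0.05, so that the level matches section 3.11.
- State that the 3-year analysis does not re-test the primary endpoint.
- State that the 80% power applies only to the 3-month endpoint at alpha 0.01.

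A fixed testing order for the later visits is optional. The cost is wording in five sections, with no new infants or data and no change to 66 and 74 per group. The small downside is that persistence to 3 years is no longer part of the powered primary claim.

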### 3.9 How will the outcome measures be measured at follow up?

The study measurements and time-lines are shown in **Tables 1-2**. At baseline (1 wk), 3, 6, 12, 24 and 36 mo of age, infants will be seen at our research unit for measurement of anthropometry, body composition and bone as well as blood sampling, skin pigmentation and surveys for diet, activity and demographic information.

**Anthropometry** - All measurements in infancy will be obtained nude and for 24 to 36 mo the child wearing standardized light clothing, dry diaper and no shoes. Weight will be taken using an electronic scale with a dynamic weighing program (Mettler-Toledo Inc., Switzerland). Length (0.1 cm) will be measured using an infantometer until 24 mo of age (O'Learly Length Boards, Ellard Instrumentation Ltd., US) and height at 36 mo will be measured using a stadiometer (Seca Medical Scales and Measuring Systems, US). Head circumference will be measured (0.1 cm) using a non-stretchable tape (Perspective Enterprises, US) to complete the anthropometric panel. Weight-for-age, height-for-age, and BMI-for-age Z-scores will be calculated using WHO software (WHO AnthroPlus, Switzerland).

**Body Composition Measurements** - Body composition will be assessed using a fan-beam DXA (APEX version 13.3:3, Hologic 4500A Discovery Series, Bedford, MA). Each infant will wear a light sleeper with no metal or plastic components and a diaper and be scanned using the infant whole body software; at 24 and 36 mo standardized light clothing will be worn and scans captured using whole body software. Whole body scans provide lean mass (g and % of weight), fat mass (g and %), BMC and BMD. Lumbar vertebra 1-4 BMC and BMD will be captured according to guidelines [2].

**Biochemistry Measurements** - Capillary blood samples (0.5 ml) will be collected at screening; but venous sampling (1.0 ml: yields ~500-600 µl serum) used thereafter; samples will be centrifuged (2235 x g for 20 min at 4°C) to obtain serum (for biochemistry) and buffy coat (white blood cells for DNA) and stored frozen at -80°C until analysis. One 5 ml sample will be taken from parents at baseline (fasting) for measurement of serum 25(OH)D and buffy coat saved for future epigenetic work. For infant screening and maternal serum, total 25(OH)D will be measured using a dedicated auto-analyzer in the PI's laboratory (25 µl; 150 µl "dead volume" that is recovered, Liaison Diasorin Inc.); this assay will also be used for safety assessments at 3 and 6 mo, but is not to be used in analyzing the trial data outcomes as it does not capture all of the metabolites. Liquid chromatography tandem mass spectrometry (LC-MS/MS by [name], Queen's Univ.) will be used to measure of 25(OH)D3, 3-epi-25(OH)D3, and 24,25(OH)2D for all time-points from baseline to 36 mo. Briefly, 100 µl of serum will be used for these assays according to our methods [3, 4]. In addition, 1,25(OH)2D (100 µl serum) will be similarly measured using an adapted LC-MS/MS method [5]. Both laboratories are certificated by the Vitamin D External Quality Assessment Scheme and will continue to participate in the National Institute of Standards and Technology quality assurance program. Blood-ionized calcium will be measured immediately using our portable unit (ABL80 FLEX Radiometer Medical A/S, Denmark) and compared to published standards [6]. Remaining sample will be used for IGF-1 (20 µl) using Liaison (Diasorin Inc.); PTH (25 µl; Immotopics Inc CAT#60-3100) and IGFBP3 (20 µl; R&D Systems CAT#SGB300) will be measured by ELISA. Sample for IGFBP3 will be pre-treated with protease inhibitors prior to storage. Plasma total calcium and phosphate (150 µl) and urinary calcium and phosphate:creatinine will be measured in a spot sample collected at each visit during the trial; Beckman Coulter UniCel Dx C600 autoanalyzer as we describe [6]. We will reserve remaining sample for later measurement of C-peptide, propeptide of type 1 collagen (P1NP) as biomarkers related to bone.

**Demographic, dietary and activity survey.** At baseline, parents will be asked to complete a demographic survey regarding their anthropometry, ethnicity and race, income and education

using the same descriptors as defined by Statistics Canada. Infant dietary intake over the study period will be assessed using 3-day diet records completed by parents after each visit as described in detail [3]. While infants are breastfed, milk intake will be assessed by test-weighing of the infant before and after breast feeding for a 24-hour period [7] using a portable electronic scale (Tanita Corporation Inc., US). This will provide nutrient intakes to help explain growth. Dietary intake from other foods is documented using household measurement items and recorded on the 3-day record. All nutrient analysis will be completed using the Nutritionist Pro software version 4.7.0 (Axxya Systems LLC, Stafford, TX) and the most recent Canadian Nutrient File database (Health Canada). At 2 and 3 y of age, the Habitual Activity Estimation Scale Questionnaire (HAES) will be completed by parents for a weekday (Tuesday, Wednesday, or Thursday) and weekend day (Saturday) over the past 2 weeks [8, 9]. Parents divide their child's day into 4 segments (wake-up to breakfast, breakfast to lunch, lunch to dinner, dinner to bedtime). For each time interval, the % time spent in each activity level is used to estimate overall level of physical activity. The 4 activity levels as established by the HAES questionnaire are: "inactive" (lying down, sleeping, resting), "somewhat inactive" (sitting, watching television, activities done mostly sitting down), "somewhat active" (walking, playing with toys), and "very active" (activities that make a child "breathe hard and sweat," like running and skipping).

***Skin pigmentation and UVB exposure*** - Skin color (type) for the infant will be established by taking the average of three measurements at each site for constitutive pigmentation at the inner upper arm and facultative pigmentation (UVB exposure) at the forehead, mid-forearm and lower leg using a spectrophotometer (CM-700d/600d, Konica Minolta, USA). Individual typological angle (ITA°) will be calculated with the L\* and b\* values using published equations [10]. Using constitutive pigmentation, infants will be classified into skin types (I-III: white; IV-VI: non-white) based on Fitzpatrick descriptions [11, 12]. Sun exposure, winter travel and use of sun block will also be surveyed. Sun exposure is expressed as a percentage of body surface area (BSA) exposed and then sun index calculated for each child by multiplying the percent BSA exposed by the time spent outside (min/d); this index does not include sun block [13]. Season of visit will be defined by equinox/solstice [14].

### 3.10 Will health service research issues be addressed?

Justify inclusion/exclusion. At this time, we will not seek these analyses. The trial is in otherwise healthy infants who are not expected to seek health services for nutritional interventions beyond the regular physician visits for routine care. Supplements for infants are covered by the Quebec Health Insurance program based on family economic status. We will document any additional testing associated with the trial such as in the event of high ionized calcium. We will record any adverse events and general illnesses. Based on our previous dose-response trial [3], we have experience with this and will document any health care use outside of routine care. This includes types of tests, duration of investigations including hospital time, parent time incurred etc.

### 3.11 What is the proposed sample size and what is the justification?

The minimum sample size (n=66) is based on the primary objective, lean mass in g at 3 mo of age and an effect size of 9% (400 g), SD of 670 g, an allocation ratio of 1:1, power of 80 and alpha of 0.01. Accounting for possible dropouts ( $\leq 10\%$ ) or missing data (1% due to movement artifact) we will study 74 infants/group. The attrition is based on 3 similar studies with an average attrition of 9% [3, 15, 16]. We have used a more stringent estimate based on an alpha of

1% to enable multiple comparisons over time and in the event of greater variability in lean mass. We believe the estimated effect size is clinically meaningful since infants in the preliminary healthy status group treated with 400 IU/d increased lean mass between 1 mo and 3 mo by 670 g and the  $\Delta$  400 g anticipated between our trial groups by 3 mo represents 60% of that normal change which would be enough to reset growth for a leaner body phenotype.

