### 3.16 What is the proposed type of analyses?

Intent-to-treat analyses. All data entry will be audited and baseline characteristics expressed as mean (SD) or median (IQR) depending on normality for continuous data or as proportions for ordinal data (e.g. white non-white, sex). Continuous data for primary outcome measurements will be expressed as mean (95% CI) or proportion (95%CI). All data analysis will be conducted using SAS (version 9.3, SAS Inst. and SAS University Edition). Continuous data for the primary outcome will be examined using mixed model ANOVA accounting for fixed effects (sex,

dosage, time, dosage\*time) and random effects (e.g. infant ID.) with post-hoc testing as applicable (i.e. 2 treatment groups and 1 reference group over 4 time-points) using Tukey-Kramer correction and significant differences accepted at  $p < 0.05$ . The mixed model ANOVA does not require that data be parametric nor of homogeneous variance. Data will be tested using Kolmogorov-Smirnov, Anderson-Darling, or a Shapiro-Wilk tests for normality and where necessary transformed (e.g. log value etc.) to meet the assumptions of the post-hoc tests. The mixed model uses all available data, missing data does not result in omission of an infant's existing data. If more than 5% of data is missing, imputation approaches will be considered. Compliance (unused product and surveyed data) will be compared between groups. For the secondary objectives, a MIXED model will be used for continuous data. The proportion of those achieving the 50 and 75 nmol/L targets will be expressed as a proportion (95% CI) and differences among groups tested using Chi-square analyses or other similar tests based on numbers in each cell or logistic regression. We are experienced in all of these tests [3, 15]. The healthy reference group will be statistically analyzed to form reference curves (e.g., lean mass) using LMS methods [18].

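### Section 3.11 sizes at a 1% level said to cover both multiplicity and a larger SD, but section 3.16 tests by a different rule; the joint margin is small and depends on the test used

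*Protocol*

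**What the plan says.** Protocol section 3.11: "The minimum sample size (n=66) is based on the primary objective, lean mass in g at 3 mo of age", with a difference of 400 g, an SD of 670 g, "an allocation ratio of 1:1" and "power of 80 and alpha of 0.01". Allowing for dropout and unusable scans, "we will study 74 infants/group". The reason given for the strict level is "1% to enable multiple comparisons over time and in the event of greater variability in lean mass". No larger SD is named, and the protocol does not say how much of the reserve goes to each purpose.

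Protocol section 3.16 analyses the primary outcome by a mixed model with sex, dosage, time and dosage-by-time as fixed effects and infant as a random effect. Post-hoc testing follows where applicable ("i.e. 2 treatment groups and 1 reference group over 4 time-points) using Tukey-Kramer correction and significant differences accepted at" p < 0.05). The 1% level does not appear there, and the 3-month contrast between the two doses is not singled out.

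**The concern.** Sizing at 1% rather than 5% buys extra infants. Section 3.11 treats those infants as protection against two separate risks: repeated testing across visits, and an SD above 670 g. Whatever the multiplicity rule uses up is no longer available for variability. Section 3.16 then fixes a rule that is not the one used for sizing. Depending on how its Tukey-Kramer family is read, that rule can be milder than 1% per comparison or about ten times stricter.

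The practical risk lies in reading a null result at 3 months. Someone relying on section 3.11 would take it as adequately powered even if lean mass proved more variable than planned. Under most ways of carrying out the written analysis, that assurance is weak or absent.

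**Working it through.** **Inputs.** From section 3.11: difference 400 g, SD 670 g, 66 evaluable per group, 1:1 allocation, power 80%, alpha 0.01. From section 3.16: p < 0.05, Tukey-Kramer, three groups, four time-points. Sidedness is not stated. Two-sided reproduces the protocol's figure, while one-sided 0.01 gives 57.

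**Reproducing the plan's figure.** n per group = 2 × (SD/difference)² × (z for alpha + z for power)².

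- Two-sided 0.01: 2 × (670/400)² × (2.576 + 0.842)² = 65.5, so 66. This matches exactly. The t-based answer is 68.
- Two-sided 0.05: 2 × (670/400)² × (1.960 + 0.842)² = 44.0, so 45.
- The stricter level therefore adds 66 − 45 = 21 per group.
- Dropout: 66/0.90 = 73.3, so 74, also as stated. The extra 8 per group are for dropout, not for variability.

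**Power at 66 per group.** The standard error is SD × √(2/66) = SD × 0.1741. The expected test statistic is 400 divided by this: 3.43 at 670 g, 3.12 at 737 g (+10%) and 2.86 at 804 g (+20%). Rows 1, 2 and 5 use the noncentral t distribution. The Tukey rows take the studentized range quantile divided by √2 as critical value c, with power ≈ Φ(expected statistic − c).

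| Rule for the 3-month dose contrast | 670 g | 737 g | 804 g | SD at which power is 80% |
|---|---|---|---|---|
| 1. Each comparison at 0.01 | 79% | 69% | 60% | 664 g |
| 2. Bonferroni, three post-baseline visits to 12 months (0.0167) | 84% | 75.5% | 67% | 702 g (+5%) |
| 3. Tukey, three groups at one visit (c = 2.36) | 86% | 78% | 69% | 717 g (+7%) |
| 4. Tukey, all 12 group-by-time cells (c = 3.28, about 0.001 per pair) | 56% | 44% | 34% | about 557 g |
| 5. One test at 0.05 | 93% | 87% | 81% | 814 g (+22%) |

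The normal approximation, which is what yields 66, gives 80%, 71% and 61% for row 1, with 80% held to 672 g. For row 5 it holds 80% to 820 g. The choice of approximation does not change the picture.

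**If nobody dropped out.** With all 74 per group evaluable and a 1% test, power is about 75% at 737 g and 66% at 804 g.

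**The case against.** A reader might infer that the design has no allowance at all for a larger SD, that the reserve cannot serve both purposes, or that the stated 80% is wrong. The documents do not support any of these.

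- **The 80% is correct on its own inputs.** Sixty-six is the exact normal-approximation answer. The gap between 79% and 80%, or between 664 g and 670 g, reflects only the t correction. The protocol also never claims 80% power at 1% for a larger SD.
- **The 1% is a planning level.** Section 3.16 declares significance at 0.05, and a single 3-month test at that level does have a 22% SD margin.
- **The reserve can be shared, modestly.** Rows 2 and 3 cover a form of multiplicity and still leave 5% to 7% on the SD.
- **The 12-cell family is one reading, and the harshest.** It includes comparisons with baseline and between different visits that answer no trial question. Section 3.16 limits post-hoc tests to those applicable, and section 2 places the reference group outside the trial. The 56% also treats the cells as independent and takes no precision gain from sex or repeated measures. The protocol gives no correlation from which to size that gain.
- **Estimates will carry 95% confidence intervals**, which would show imprecision in a null result.

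All of this stands. It does not remove the mismatch between the two sections, and the wording of section 3.16 does allow the 12-cell reading. The large margin in row 5 exists only if multiplicity is handled by some means other than the 1% level.

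**Conclusion.** The point holds in a limited form. Section 3.11 sizes at one level and gives it two purposes, while section 3.16 tests by another rule. The joint margin is small and unquantified: essentially nil if each comparison is at 1%, and 5% to 7% on the SD under the milder adjustments. Under Tukey over 12 cells, the protocol's own SD gives about 56% rather than 80%. Only an unadjusted 3-month dose contrast at 0.05 has a substantial margin. At a 1% test, keeping 80% power with a 10% larger SD would need 80 evaluable infants per group.

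These figures assume a two-sided test, 66 evaluable per group, a between-infant comparison at 3 months, and no variance reduction from the mixed model. The 12-cell figure is approximate.

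**What to change.** Align sections 3.11 and 3.16.

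1. Name the 1000 versus 400 IU/d contrast in lean mass at 3 months as the primary test at two-sided 0.05, outside the all-pairs Tukey family and without reference-group comparisons.
2. State one multiplicity rule for the later visits. Testing them in a fixed order is one option among several valid ones.
3. Replace the dual-purpose sentence in 3.11 with power over a range of SDs at the level actually used. At 0.05 with 66 per group this is about 93% at 670 g, 87% at 737 g and 81% at 804 g.

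If the 1% level or the 12-cell Tukey is kept instead, restate the power at SD 670 g as about 79% or about 56% respectively, and drop the claim that a larger SD is covered.

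The cost is wording only, with no extra infants. Later-visit and reference-group comparisons become secondary.
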